### Objective 2: Ascertainment

Our second hypothesis is that intervention implementation improves ARA ascertainment.

Patients attending ED can do so repeatedly within periods of time. This frequency is likely associated with the modifiable risks associated with ARA and is of interest here. For Objective 2 it is therefore appropriate to determine the proportion of attendances identified as violence related. This generates time-series data. The outcome of interest is therefore the count of ARAs across all EDs. ARA attendance is defined as ARA in the ED PMS or, in the case of intervention sites, in the ED, PMS, or VPT data. Codes indicating the Provider Site (the ED in its hospital) are available in the EDDS, and this allows comparison between intervention EDs and control EDs. While intervention EDs have been in continual service since before the time-series start dates, this is not so for all Type I EDs in Wales; there have been several changes, with some EDs closing and others opening or being modified to receive additional patients. This, coupled with the intervention sites located at two of the largest hospitals in Wales, reduces the scope for selecting matching control sites [40], leading to potentially important baseline differences in the interrupted time-series data [41]. The counterfactual will therefore be ARAs across all control Type I EDs.

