**Methods:**

ED patients are eligible for inclusion in the evaluation if they are normally resident in Wales, United Kingdom, aged 11 years and older. A controlled longitudinal natural experiment will be undertaken. The primary outcome is derived from the Emergency Department Dataset, routinely collected for all EDs in Wales, and is subsequent unplanned ED attendance. Case patients will be matched to control patients attending EDs without an HVIP. Analysis will derive the hazard rate for subsequent unplanned ED attendances using recurrent event analysis. The total monthly count of patients identified as attending because of violence in intervention EDs will be compared to the total count of Welsh control EDs in an interrupted time-series analysis to determine whether HVIPS increase violence ascertainment. To determine whether referral, versus no referral, to the HVIP represents value for money, we will undertake a cost-effectiveness analysis from the perspective of the National Health Service. The approval to access and analyze data housed in the Secure Anonymized Information Linkage (SAIL) databank, an ISO (International Organization for Standardization) 27001 certiﬁed and UK Statistics Authority accredited secure data environment, was granted by the SAIL independent Information Governance Review Panel (Ref: 1421). Findings will be presented at local, national, and international conferences and disseminated by peer-reviewed publication.

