EDs work with patients attending for many reasons, including those presenting with violence-related injuries. EDs also engage in broader violence reduction initiatives, clinical staff typically receive training in adult and pediatric safeguarding, and many EDs have provisions to identify and refer children and victims of domestic and sexual violence. However, methods of ascertainment and referral vary considerably, and formal relationships with the police and other partners can often lack continuity, with multiagency approaches not capturing the entirety of patients’ journeys. A public health approach involving the ED would be beneficial in improving overall population health outcomes. It is particularly timely; in 2019 there were 175,764 ARAs at EDs in England and Wales [11] and, despite the pandemic, 119,111 ARAs in 2020 [12]. Knife crime, and therefore serious trauma, has risen by 71% from 2014 to 2018 [13]. Up to 75% of ARAs are unknown to the police [14-16]; therefore, EDs hold exclusive data on assault characteristics, patient vulnerabilities, and modifiable risks and are therefore well situated to play a significant role in the identification of violence, to investigate the circumstances of violence, and to challenge any underlying vulnerabilities or modifiable risks exposing patients to violence, whether that is through direct support, referral, or discharge planning.

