#### Objective 2: Ascertainment

The hypothesis is that a violence attendance is more likely to be ascertained as such with the additional VPT resource present in ED. All unplanned attendances can be coded as ARA or not (1, 0). The time series begins in January 2012, and the 2 sites (Cardiff and Swansea) can be individually compared with all other Type I EDs in Wales. This indicates that a difference-in-difference model [59] is appropriate. We will analyze Cardiff first, using the implementation in Swansea as a future replication of the intervention to facilitate a more robust causal interpretation of any effect. Additional descriptive analysis can explore patient groups (age, gender, and time of attendance) more likely to be ascertained by the VPTs. Unlike Objective 1, we are interested in all ED attendances, as the opportunity to provision safeguarding is applicable across all ED attendances, irrespective of the frequency of attendance.

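### Objective 2 argues for the proportion of attendances but fixes a raw count of ARAs, so differential changes in ED volume are confounded with ascertainment

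*Protocol article*

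**What the plan says.** Three places in the protocol article describe the Objective 2 outcome, and they do not agree.

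- **Design and Conceptual Framework, Objective 2: Ascertainment.** Because patients can attend repeatedly, the text says "it is therefore appropriate to determine the proportion of attendances identified as violence related". Two sentences later it concludes "The outcome of interest is therefore the count of ARAs across all EDs". The comparator is also a count: "The counterfactual will therefore be ARAs across all control Type I EDs".
- **Abstract, Methods.** The unit is the patient and the measure a total: "The total monthly count of patients identified as attending because of violence in intervention EDs will be compared to the total count" for the Welsh control EDs, in an interrupted time series.
- **Analytic Strategy, Objective 2: Ascertainment.** The unit is the attendance: "All unplanned attendances can be coded as ARA or not (1, 0"). The hypothesis is that a violence attendance is more likely to be recognised when the team is present. A difference-in-difference model is named. Its scale is not given, and total attendances are not named as denominator or offset.

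The first of these sections also reports that, unlike the intervention departments, not all Type I departments in Wales ran throughout the series: some shut, some opened, and some were altered to take more patients. It accepts that baseline differences may matter. The Conclusion calls this objective a primary outcome; Principal Findings calls it exploratory.

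**The concern.** The count does not follow from the sentence that leads to it. Repeat attendance is a reason to analyse attendances rather than patients, and the text draws from it that a proportion is wanted. A count without a denominator is a different quantity.

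The choice matters because the hypothesis is about a probability per attendance. A department that receives more patients records more assault-related attendances even if staff recognise violence exactly as before. Where volume changes differently in the intervention and control groups, a comparison of counts attributes that difference to the Violence Prevention Team. The article's account of departments shutting, opening and expanding on the control side only makes such a difference plausible. The estimate could then be too large, too small, or of the wrong sign.

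**Working it through.** The article gives no effect size, power or expected count for Objective 2, so there is no stated figure to reproduce. The check is algebra with labelled assumptions.

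**1. What each measure contains.** For one site-month let N be all unplanned attendances, p the share truly due to assault, and a the probability that such an attendance is coded as ARA. Ignoring false positives:

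- ARA count = N × p × a
- ARA proportion = p × a

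On the ratio scale, with each term the intervention-to-control ratio of post/pre changes:

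- count comparison = (change in N) × (change in p) × (change in a)
- proportion comparison = (change in p) × (change in a)

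Only the change in a is ascertainment. The proportion removes N; it does not remove p.

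**2. Differential volume.** Hold p and a constant, so the true answer is 1.00, and let intervention volume change by g relative to control (g is assumed; the article gives no volumes).

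| g | count ratio (1 + g) | proportion ratio |
|---|---|---|
| −20% | 0.80 | 1.00 |
| −10% | 0.90 | 1.00 |
| +10% | 1.10 | 1.00 |
| +20% | 1.20 | 1.00 |

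**3. Does pooling the controls solve this?** Patients who move from one control department to another stay in the pooled total, so that shift cancels. A move from a control to an intervention department does not. With assumed monthly counts of 100 (intervention) and 400 (pooled control), moving 10 ARAs across gives (110/100) / (390/400) = 1.10 / 0.975 = 1.13, with no coding change. A net gain or loss of capacity on the control side does not cancel either.

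**4. The 2020 fall.** Background gives 175,764 ARAs in 2019 and 119,111 in 2020 for England and Wales: 1 − 119,111/175,764 = 32.2%. Cardiff started in November 2019 (Design and Conceptual Framework), so 2020 lies in its post-implementation period. Suppose the fall is the same everywhere and ascertainment does not change:

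- ratio scale: 0.678 / 0.678 = 1.00, no bias;
- additive scale, control total r times the Cardiff count: spurious gain = 0.322 × (r − 1) of Cardiff's baseline, which is 0 at r = 1, 97% at r = 4 and 258% at r = 9 (all r assumed).

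**5. Does the proportion remove the fall?** Not by itself. With ARAs down 32.2% and all attendances down by v (assumed), the proportion in a single ED series changes by 0.678 / (1 − v): 0.68 at v = 0, 0.75 at 10%, 0.85 at 20%, 1.00 at 32.2% and 1.13 at 40%. The control series is still needed, and a fall that differed between sites would remain.

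**The case against.** Five points can be made for the plan.

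- **The analytic section may already mean a proportion.** It codes all unplanned attendances 1/0, and the mean of that indicator is the proportion. This is a fair reading, but it conflicts with the outcome and counterfactual fixed earlier and with the abstract. It supports reconciliation; it does not remove the conflict.
- **Pooling is the stated answer to openings and closures.** It works for shifts among control departments. It does not work for shifts across the two groups or for net changes in capacity (step 3).
- **A proportion has its own weakness.** The section on discontinuous risk intervals notes that conveyance initiatives and community alternatives for lower-acuity patients may differ across Local Health Boards. These would change total attendances, and so the proportion, with no change in coding. This stands, and is why both measures should be reported.
- **Scale, offset and model terms belong in the full protocol or analysis plan.** Their absence from a condensed article is not the criticism. The criticism is that the article states the outcome, and states it inconsistently.
- **The pandemic is not a fault of choosing a count.** This is right. A reader might infer that the 2020 fall must appear as an ascertainment effect, or that the Cardiff estimate is inflated by about 97%. The documents do not support either. The 97% needs an additive model the article never states, an assumed fourfold control total, and a one-year figure for England and Wales applied to Welsh departments over the whole post period.

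**Conclusion.** The inconsistency is in the text: a proportion is argued for, a count is fixed, the abstract counts patients and the analytic section codes attendances. If the count is followed as written, ascertainment is confounded with any differential change in ED volume, one for one on the ratio scale: 0.80 to 1.20 for an assumed relative change of −20% to +20%, where the proportion would give 1.00. That 1.00 rests on a constant assault share. The article makes a differential change plausible but gives no volumes, so neither the direction nor the size of any actual bias can be stated.

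The 2020 fall is a secondary matter. It biases the Cardiff comparison only if the model is additive on unequal totals or if the fall differed between sites. Adding a denominator does not cure the second case.

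**What to change.** Reconcile the abstract and both Objective 2 sections to one unit and one outcome:

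- **Unit:** attendances, as the article's own argument about repeat attendance implies.
- **Outcome:** ARA-coded unplanned attendances per site-month, with total unplanned attendances as the binomial denominator or as a log offset in a count model.
- **Model:** site intercepts, so that departments that open or shut enter as series of unequal length, and a comparison stated on the ratio scale.
- **Sensitivity analysis:** keep the raw count and report it beside the proportion. If the two diverge, volume or case mix has changed, and the reader can see it.
- **Secondary suggestion:** one further sensitivity analysis that omits 2020 or adds a pandemic term specific to each site group.

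The data cost is low, because the analytic section already codes every unplanned attendance and so the denominator exists. A pandemic term would cost some precision for Cardiff. The Results section says that the Objective 2 analyses were completed in July 2025 and are published. Any re-run should therefore be labelled post hoc, and the authors should state which outcome was prespecified in the full protocol.

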### Intervention as Implemented

Since November 2019, a collaborative VPT between the police and NHS has been operational in a South Wales Type I (consultant-led with resus) ED in Cardiff (the capital and largest city in Wales), and a second VPT began in an adjacent South Wales Type I ED in Swansea (the second-largest city in Wales) in January 2022. The VPTs initially sought to identify patients attending the ED due to violence. This remit was broadened, with VPTs subsequently receiving referrals from across the hospital and other community health care teams (eg, Minor Injury Units [MIUs] and General Practitioners).

The VPTs work with patients to gain an understanding of any circumstances contributing to their exposure to violence. They refer patients into care pathways (primary, secondary, and tertiary care, or third-sector organizations) to address any vulnerabilities or modifiable risks and can work alongside the third sector (nonprofit and charitable enterprise) to provide continual case management. The VPTs also train other staff within the hospital to improve the identification of violence-related injury, to support clinical staff interactions with patients, and to maintain safeguarding procedures. In addition, the EDs at Cardiff and Swansea take part in information sharing to tackle violence, in which anonymous data and intelligence regarding violent incidents are shared with community safety partnerships. These anonymized data enable partner resources to be best used for violence prevention, part of the Cardiff Model for violence prevention [39]. Following implementation, both VPTs expanded the age range of patients to encompass all age groups.

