### Design and Conceptual Framework

A controlled longitudinal whole population (Wales, United Kingdom) natural experiment. The intervention in Cardiff began in November 2019, and in January 2022 in Swansea. Due to earlier changes in Emergency Department Data Set (EDDS) coding, these data are consistent and available from January 2012. Intervention data collection therefore begins in November 2019 and ends in August 2023, allowing a 12-month follow-up of patients until August 2024.

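### Objective 2 adds a second source of assault-related attendances (ARAs) only at intervention EDs and only from launch, so the comparison cannot separate the VPT's own case-finding from better ED coding

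*Protocol article*

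**What the plan says.** Under Design and Conceptual Framework, the Objective 2 section of the protocol article gives the outcome definition: "ARA attendance is defined as ARA in the ED PMS or, in the case of intervention sites, in the ED, PMS, or VPT data". It then sets the measure, "The outcome of interest is therefore the count of ARAs across all EDs", and the comparator, "The counterfactual will therefore be ARAs across all control Type I EDs". Just before adopting counts, it says that the proportion of attendances identified as violence-related is the appropriate quantity. It also reports that some Type I EDs closed, opened or were altered to take more patients during the series.

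Under Analytic Strategy, the hypothesis is that "a violence attendance is more likely to be ascertained as such with the additional VPT resource present in ED". The model is a difference-in-difference, every unplanned attendance can be coded 1 or 0 for ARA, and "The time series begins in January 2012". On launch dates, Design and Conceptual Framework says: "The intervention in Cardiff began in November 2019, and in January 2022 in Swansea".

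The article states no PMS-only analysis for Objective 2 and describes no parallel second source at control EDs.

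**The concern.** A difference-in-difference estimate assumes that the outcome is measured in the same way in both groups and both periods, or at least that any change in measurement is shared. Here the change in measurement coincides with the intervention in place and in time. Subtracting the control series cannot remove it, because the control EDs have no equivalent log.

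The VPT is expected to raise ascertainment by two routes. It finds cases itself, and it trains ED staff to recognise and record violence (Intervention as Implemented). A service deciding whether to adopt a VPT would want to know which route works. With the combined outcome, a positive estimate is compatible with staff coding that did not change at all.

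The use of counts is a second, smaller problem in the same definition. A count moves with attendance volume as well as with the chance that a violent attendance is recognised.

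**Working it through.** **Set logic.** Let P be the PMS-coded count and V the number of cases found only in VPT data. At an intervention ED the outcome is P before launch and P + V after it. At control EDs it is C throughout. On the count scale:

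estimate = [(P_post + V) − P_pre] − [C_post − C_pre] = PMS-only estimate + V, with V ≥ 0.

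On the ratio scale, the PMS-only rate ratio is multiplied by 1 + V/P_post. The added term is zero only if every VPT case is already in the PMS.

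**Are VPT-only cases expected?** Objective 1 (Design and Conceptual Framework) says that patients may not disclose assault at reception, where the PMS field is filled. Its second group is defined by PMS or VPT data, which allows for patients seen only by the VPT. Its third group, those who engaged, is defined by PMS and VPT data together.

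**Size in Cardiff.** The article gives no baseline count, effect size or power for Objective 2, so there is no stated figure to reproduce. Sampling gives 2312 contacts from October 2019 to December 2022, of whom 77% accepted support.

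- Months: 3 + 12 + 12 + 12 = 39. Contacts per month: 2312/39 = 59.3.
- Read literally, the grouping places engaged patients in both sources. VPT-only cases can then come only from the 23% who did not engage: 0.23 × 2312 = 532, and 532/39 = 13.6 a month.
- Counting from the stated November 2019 start gives 38 months and 532/38 = 14.0 a month.

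The range is therefore 0 to about 14 a month.

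**Relative size.** The baseline PMS count is not given, so 100 to 300 ARAs a month is assumed. With PMS coding unchanged, the rate ratio is 1 + V/baseline:

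| VPT-only share of contacts | V per month | Baseline 100 | Baseline 200 | Baseline 300 |
|---|---|---|---|---|
| 0% | 0 | 1.00 | 1.00 | 1.00 |
| 5% | 3.0 | 1.03 | 1.015 | 1.01 |
| 10% | 5.9 | 1.06 | 1.03 | 1.02 |
| 23% (ceiling) | 13.6 | 1.14 | 1.07 | 1.05 |

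**Could this be declared an effect?** A Poisson simulation held PMS coding constant over 94 months before launch (January 2012 to October 2019) and 46 months after it (November 2019 to August 2023). It assumed a control total of 500 a month and used 4000 runs with a two-sided 5% test. The hypothesis of no change was rejected as follows:

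| VPT-only share | Baseline 100 | Baseline 200 |
|---|---|---|
| 0% (same source throughout) | about 5% | about 5% |
| 5% | 33% | 16% |
| 10% | 84% | 51% |

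The simulation ignores overdispersion and autocorrelation, so these rates are only indicative.

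**Counts against proportions.** An ARA count is attendances multiplied by the proportion coded ARA, so on the log scale a change in the count is the sum of the two changes. Moves between control EDs cancel in the pooled control total. Moves between control and intervention EDs, or into and out of Type I provision, do not.

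**The case against.** The strongest reply is that a case found only by the VPT is the effect under test. The hypothesis concerns the VPT being present in the ED, and the Introduction describes identifying assault patients as part of the team's main function. A PMS-only outcome would omit non-disclosers found later by the VPT unless the PMS is updated, and so would answer a narrower question. Much of this stands. For genuine ED attenders the combined count is a legitimate quantity and should be kept. It does not justify using that count as the only comparison, because the two routes are mixed and control EDs have no equivalent log.

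Four stronger readings are tempting, but the article does not support them.

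- A reader might infer that a positive result is guaranteed. It is not: VPT cases may already be in the PMS, and PMS counts may fall after launch.
- A reader might take half of all contacts as VPT-only, about 30 a month. That exceeds the ceiling of about 14 a month implied by the article's own grouping.
- A reader might infer that each VPT site sits in the other's comparator, because each site "can be individually compared with all other Type I EDs in Wales". The Abstract, Usual Care and the stated counterfactual all treat control EDs as separate from Cardiff and Swansea.
- A reader might infer that non-ED referrals inflate the count, given "with VPTs subsequently receiving referrals from across the hospital and other community health care teams". The coded unit is the unplanned attendance, and Allocation requires intervention patients to have attended an intervention ED. The Objective 2 definition does not repeat that limit, so it is worth stating, but inflation is not shown.

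It is also fair to say that the Discussion calls Objective 2 exploratory (although the Conclusion calls it a primary outcome), and that the full protocol is not shown and may contain sensitivity analyses.

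**Conclusion.** The concern holds as one of differential measurement. The outcome source changes only at intervention EDs and only at launch, in the direction of the hypothesis. A positive estimate could therefore arise with unchanged ED coding, and it could not show how much is direct VPT case-finding and how much is better identification by staff.

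In Cardiff the added cases lie between 0 and about 14 a month. That ceiling assumes that accepting support means engaging, that engaged patients are in both sources as the grouping says, and that the contacts represent the VPT records. The true VPT-only share is not stated. The article gives no corresponding number of contacts for Swansea. The relative sizes and rejection rates also depend on assumed baseline and control counts.

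The switch from proportion to count is a separate, smaller inconsistency within the same section. Its effect cannot be sized from the article.

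**What to change.** Run the between-site comparison on ARAs coded in the PMS/EDDS, with one definition for all sites and all months. Model ARAs per unplanned attendance, either as binomial using the 1/0 coding already described or as counts with an attendance offset.

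Beside it, report the PMS-or-VPT result, limited to VPT records linked to an ED attendance at that site. Label it as including direct VPT case-finding, and show the VPT-only share by site and over time. The two results together answer both the broader and the narrower question.

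The data are already held. The cost is a probably smaller estimate and some further work: the Results section says that the Objective 2 analyses were completed in July 2025 and are published, so this means a re-run or a supplementary report. If the full protocol or the completed analysis already contains a PMS-only result, citing it and giving the VPT-only share would settle the source question.

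### Objective 2 compares each VPT site with one pooled count over a changing set of control EDs, so a net change in the controls can bias the estimated effect on ascertainment

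*Protocol article*

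**What the plan says.** The Abstract (Methods) plans to take the monthly count of violence attendances in intervention EDs, which "will be compared to the total count of Welsh control EDs in an interrupted time-series analysis".

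The section Objective 2: Ascertainment, under Design and Conceptual Framework, notes that the intervention EDs were in service throughout, but that the same cannot be said of every other Type I unit, where "there have been several changes, with some EDs closing and others opening or being modified to receive additional patients". It adds that the intervention sites are among the largest hospitals, which leaves little scope for matched control sites, and concludes: "The counterfactual will therefore be ARAs across all control Type I EDs". The same section gives two outcome scales. It says "it is therefore appropriate to determine the proportion of attendances identified as violence related", and shortly afterwards "The outcome of interest is therefore the count of ARAs across all EDs". It also says that "Codes indicating the Provider Site (the ED in its hospital) are available in the EDDS".

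Under Analytic Strategy, Objective 2, the series starts in January 2012. Cardiff and Swansea "can be individually compared with all other Type I EDs in Wales" by difference-in-difference, with Cardiff analysed first and Swansea serving as a replication. No section adjusts for the changing control set.

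**The concern.** A difference-in-difference reads any movement in the control series as what would have happened at the VPT site without the VPT. That works only if the control series measures the same thing before and after launch. Here the article itself says that the set of control EDs changed while the treated EDs did not.

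A single pooled count leaves three routes open:

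- patients enter or leave the control Type I series altogether, for example to or from a minor injury unit;
- patients move between a control ED and Cardiff or Swansea, which shifts both arms in opposite directions;
- patients move between control EDs that record assault differently, so the pooled figure changes with no change in violence.

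Each could be read as a gain or loss in ascertainment caused by the VPT. The article's Conclusion calls this outcome primary, although Principal Findings calls the objective exploratory.

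**Working it through.** **Nothing to reproduce.** The article gives no sample size, power or expected effect for Objective 2. The check asks what the planned comparison returns when the VPT has no effect.

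**Inputs from the article.** The series starts in January 2012. Cardiff launches in November 2019, so there are 7 × 12 + 10 = 94 months before it. Intervention data end in August 2023, giving 2 + 36 + 8 = 46 months after it. Swansea launches in January 2022, 26 months after Cardiff. Usual Care mentions 10 control EDs, without dating them or labelling them Type I.

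**Assumptions, not in the article.** 100 ARAs a month at the intervention ED and 600 in the pooled controls (10 equal sites of 60). For the proportion scale, 2% of attendances at the other control EDs are ARAs.

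**Formula.** Ratio = (I1/I0) / (C1/C0), where I and C are intervention and control levels before (0) and after (1). With no VPT effect it should be 1.

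1. *Transfer wholly between control EDs that record alike.* C1 = C0, so the ratio is 1.00. Pooling works here.

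2. *Net loss of a fraction f from the control count.* Ratio = 1/(1 − f): 1.05, 1.11 and 1.25 for f = 5%, 10% and 20%. A net gain gives 1/(1 + f): 0.95, 0.91 and 0.83.

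3. *One of ten equal control EDs closes and part of its load goes to the intervention ED, the rest to other controls.* With 25% (15 ARAs): (115/100)/(585/600) = 1.18. With 50% (30 ARAs): (130/100)/(570/600) = 1.37.

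4. *Proportion scale, one of ten equal sites leaves the series.* The pooled control proportion goes from (9 × 2% + p)/10 to 2%, where p is the closed site's proportion. For p = 1%, 2% and 3%, the ratios are 1.9/2 = 0.95, 2.0/2 = 1.00 and 2.1/2 = 1.05. The corresponding count ratios are 1.06, 1.11 and 1.17.

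5. *Proportion scale, patients stay within the controls but the closed site recorded at r times the others' rate.* With volume share s, the pooled control figure changes by 1/(s·r + 1 − s) − 1.

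| s | r = 0.5 | r = 2 |
|---|---|---|
| 10% | 1/0.95 − 1 = +5% | 1/1.10 − 1 = −9% |
| 20% | 1/0.90 − 1 = +11% | 1/1.20 − 1 = −17% |

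The false VPT ratio is the inverse: 0.95 or 1.10 for 10%, and 0.90 or 1.20 for 20%.

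6. *Timing.* Poisson models with Pearson scale, 400 simulated series per setting, no VPT effect, 10% net control loss on the count scale:

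| Control loss occurs | Simple difference-in-difference: ratio (rejected at 5%) | With group-specific trends: ratio (rejected) |
|---|---|---|
| Month 60, before launch | 1.07 (84%) | 0.97 (13%) |
| At Cardiff launch | 1.11 (99.8%) | 1.11 (86%) |
| 12 months after launch | 1.08 (95%) | 1.06 (37%) |
| No loss | about 1.00 (5–7%) | about 1.00 (4–6%) |

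These series have no underlying trend or seasonality, so the rejection rates show the mechanism and do not predict the real analysis.

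**The case against.** **Pooling is a deliberate response.** Closures, openings and sites enlarged to take more patients read at least partly as redistribution, and a pooled total absorbs redistribution among control EDs. This stands, provided the EDs concerned record ARAs similarly. A reader might infer that every control-site change distorts the estimate. The article does not support that, and step 1 shows the contrary.

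**The remaining routes are not documented.** The article does not say that a closed site's patients left the Type I system or went to Cardiff or Swansea, nor that any change fell near a launch. It gives no site volumes and no recording rates by site, and it describes the ED dataset as consistent from 2012. This stands as a limit on size. The routes are still plausible on the article's own account: Discontinuous Risk Interval describes minor injury units and onward referral to Cardiff and Swansea, with a patient registered at more than one ED, and Background says ascertainment methods vary considerably between EDs.

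**A proportion softens the problem.** True: step 4 falls from 1.11 to 1.00 when sites are alike. It does not remove the bias when they differ, and the article also names a count.

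**Swansea is a replication.** A reader might infer that control changes destroy its value. They do not: a change at one date is unlikely to match two launches 26 months apart. The replication lowers the risk, but both comparisons use the same pooled controls, so it does not remove it.

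**Model detail belongs in the analysis plan.** Site terms could be there and would not be a finding if merely absent here. The pooled count, however, is stated here as the rule, and following it can give a wrong estimate.

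**Conclusion.** The concern holds in a limited form. The stated counterfactual is a pooled count over a control set that the article says changed, and nothing stated corrects for a net change in that set, flows to or from the VPT sites, or a changing mix of recording practice. Any of these can bias the estimated VPT effect upward or downward, most of all near a launch date.

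The real size is unknown. A 10% net control loss would give a false ratio of about 1.11 on counts. On proportions, losing a site with 10% of volume would give 0.95 to 1.05 if its ARA proportion differed by half from the others'. The larger figures in the working need a site with 20% of control volume, a twofold difference in recording, or substantial diversion to the VPT site. A reader might infer that the Objective 2 result is wrong by such amounts. The article gives no dates or volumes that would support this, and it does not present the results.

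**What to change.** 1. Settle the outcome as the proportion that the article itself calls appropriate: ARAs over unplanned attendances.
2. Fit a site-by-month difference-in-difference with site fixed effects and common month effects, using the Provider Site codes. Each site contributes only while open.
3. Add step terms at continuing control sites that were modified or took on a closed site's patients. Do not put a step at a site's own opening or closure: if the site contributes only while open, that step cannot be separated from its site effect.
4. Report this beside the pooled analysis, with a dated list of control-site openings, closures and modifications.
5. Give an analysis restricted to continuously open control EDs only as a further check, noting that it keeps the sites that inherited patients.
6. List and test separately any change that moved patients to or from Cardiff or Swansea, because site effects do not correct those flows.

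The Results section says the Objective 2 analysis was completed in July 2025 and published, so this would be a reported re-analysis or sensitivity analysis. The attendance data and site codes are already available. The cost is extra programming, obtaining the dates of the site changes, and possibly wider intervals.
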